#### Secondary outcome measures

The following measures will also be used. Sequentially, resting blood pressure will take place prior to the finger-prick blood sample and then the physical measures. Questionnaires will be done during the assessment session.

1. The Short Version of the Depression Anxiety Stress Scale (DASS-21) has 21 items and consists of three subscales: depression, anxiety and stress [33]. Items ask respondents to indicate the frequency of intra-personal experiences, such as finding it hard to wind down, on a four point Likert scale (0 *not at all *to 3 *most of the time*). Each subscale has demonstrated high internal consistency and yielded meaningful discriminations in a variety of settings in both Australian clinical and community samples [33].

2. Physical activity participation will be assessed via self-report using items adapted from the Active Australia surveys to assess the total time spent during the last week (i) walking briskly for recreation or exercise (adapted to exclude walking to get to and from place to place), (ii) doing moderate physical activity, like social tennis, swimming, golf, (iii) doing vigorous physical activity like aerobics, cycling, running [34]. Two additional items will be used to assess total time spent walking for transport and cycling for transport. Total time spent in recreational physical activity will be calculated by summing time spent in minutes across the three categories, with time in vigorous activity weighted by a factor of two to reflect greater intensity i.e., Σ[minutes walking + minutes moderate activity + (minutes vigorous activity × 2)]. Total time spent in transport activity will be calculated by summing time spent in minutes of walking and cycling for transport. Physical activity will also be assessed using pedometer step counts. Participants will be asked to wear a pedometer for seven consecutive days and record the total number of steps taken each day; this data will be used to derive average daily step counts.

3. Physical indicators of CHD risk. Resting blood pressure will be assessed via an aneroid sphygmomanometer (Alpk2 Aneroid sphygmomanometer, Model No. 500-V, Japan), with two measures taken at least one-minute apart, and the average of the readings used in the analyses [35]. If the variation between the two measures exceeds 5%, a third measure will be taken in order to reduce any potential measurement error. Waist circumference will be measured in duplicate at the narrowest point between the lower rib and the iliac crest at the end of a normal expiration [36] with a flexible steel tape (F10-02, KDS, Japan) by an ISAK-accredited Level 1 Anthropometrist. If the variation between two measures exceeds 5% a third measure will be taken in order to reduce any potential measurement error. Body mass index will be calculated using height measured using a portable stadiometer (Portable Height Scale, Mentone Educational Center, Australia) to the nearest 0.01 m and body weight to the nearest 0.1 kg via calibrated bioelectrical impedance scales (Tanita TBF-521, Tanita Corporation, Tokyo).

4. Hemotological measures will be assessed using a 35 μl capillary blood sample drawn from a finger prick blood sample for immediate analysis via a Cholestech LDX system (Cholestech LDX, Cholestech, USA). Each capillary blood sample will be analyzed for random blood glucose (mmol·L^-1^), total cholesterol (mmol·L^-1^), HDL-cholesterol (mmol·L^-1^), LDL-cholesterol (mmol·L^-1^) and triglycerides (mmol·L^-1^).

5. Somatic complaints. Participants will be asked to indicate on a five point Likert scale (1 *rarely or never *to 5 *almost daily*) how often they were distressed by each of 14 somatic complaints, such as sleep difficulties, muscular tension, headaches and stomach pains.

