#### Group 2: READY resilience program plus physical activity promotion

Participants will receive the resilience training described for Group 1, as well as an additional session and ongoing content promoting physical activity. The session will include psycho-education on physical activity and resilience; a review of national physical activity guidelines; discussion of step counting and pedometer use; consideration of preferred types of physical activity; goal setting; strategies to redress barriers to physical activity, and planning and problem solving for relapsing participation. Walking, both purposive and incidental, will be specifically promoted as a physical activity option requiring no resources. Participants will be given a pedometer (step counter) and logbook, and will receive instruction and rehearsal on how to wear and use the pedometer for self-monitoring. Subsequent sessions will include a check on progress with physical activity goals, and discussion on how to apply resilience strategies to facilitate physical activity participation e.g., obtaining social support, identifying associated values, using cognitive strategies to redress negative thoughts.

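### The vigorous-activity item names cycling without excluding cycling for transport, so commuting minutes can enter both the recreational total (weight 2) and the transport total (weight 1)

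*Protocol article*

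**What the plan says.** All of this is in the protocol article, Secondary outcome measures, item 2. Recreational activity is asked in three categories.

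- The walking category is "walking briskly for recreation or exercise (adapted to exclude walking to get to and from place to place".
- The moderate category gives examples such as social tennis.
- The vigorous category is "iii) doing vigorous physical activity like aerobics, cycling, running".

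The plan then adds transport: "Two additional items will be used to assess total time spent walking for transport and cycling for transport".

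Two scores follow. The first, for recreational activity, adds up the three categories with vigorous minutes counted double, and is written as "Σ[minutes walking + minutes moderate activity + (minutes vigorous activity × 2". For the second, "Total time spent in transport activity will be calculated by summing time spent in minutes of walking and cycling for transport". The two scores are not added together. A week of pedometer wear supplies a third activity measure, mean steps per day.

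**The concern.** Splitting activity into a recreational and a transport score works only if each minute belongs to one of them. The plan secures this for walking by taking travel out of the recreational item. It does not do so for cycling, which is a named example of vigorous activity and also has its own transport item. As described, the wording lets a respondent put a ride to work under the vigorous item, the transport item, or both.

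Two things would follow. Commuting could appear in a score labelled recreational, and it would do so at double weight. The same behaviour could also give different scores in different people, or in one person at different assessments. Item wording cannot be repaired after collection, because the answers do not show which reading each respondent used.

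**Working it through.** The article gives no activity data and no target difference for activity, so there is no figure of the plan's own to reproduce. Its sample size of 28 per group rests on Ryff's scales and does not bear on this point.

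**Inputs from the article (Secondary outcome measures, item 2)**

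- Recreational total: R = W + M + 2V, where W is recreational walking, M moderate and V vigorous minutes.
- Transport total: T = TW + TC, where TW is transport walking and TC transport cycling minutes.
- W excludes travel. V has no stated exclusion.

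**Assumed behaviour:** 100 min/week of cycling to work and no other activity.

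| How the respondent reads the items | V | TC | R = 2V | T = TC |
|---|---|---|---|---|
| Transport item only | 0 | 100 | 0 | 100 |
| Vigorous item only | 100 | 0 | 200 | 0 |
| Both items | 100 | 100 | 200 | 100 |
| With a travel exclusion in the vigorous item | 0 | 100 | 0 | 100 |

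The true recreational time is 0 in every row. Under the current wording R is 0 or 200, and T is 0 or 100. With the exclusion, one reading remains.

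**Effect on an arm mean at one time point.** Assume one person who cycles 200 min/week (20 min each way, 5 days: 20 × 2 × 5) and reports it under both items. R is 2 × 200 = 400. In an arm of 32, within the planned 30 to 35, the mean rises by 400/32 = 12.5 min/week. The range is 400/35 = 11.4 to 400/30 = 13.3.

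**Effect on change from baseline.**

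- Same cycling, same reading at both times: 200 − 200 = 0 for the 100-minute rider. The error cancels.
- Same cycling, but both items used at baseline and only the transport item later: 0 − 200 = −200 on R with no change in behaviour.
- Cycling falls from 60 to 0 min, both items used throughout: R changes by 0 − 120 = −120, although recreational time did not change.

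What survives comparison with baseline is therefore a change in reading or a change in cycling, not stable misreporting.

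**Walking, as a contrast.** Add 60 min of transport walking to 60 min of recreational walking: R stays at 60 and T goes from 0 to 60. Each minute enters one total, as the plan intends.

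**The case against.** The article is a summary, and the printed questionnaire is not shown. It may already tell respondents to leave travel out of the vigorous item, and a respondent who also meets a separate transport-cycling item may enter commuting only there. Double reporting is therefore possible, not established. The two totals are never added, so no single score contains the same minutes twice. Outcomes are compared across three assessments, which removes most stable misreporting, and nothing in the article suggests that the reading of the item would differ by arm. All of this stands and limits the weight of the point. It does not remove the mismatch: the article reports an exclusion for walking and none for cycling.

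A reader might go further and infer that the activity outcome misses what Group 2 is taught and could move the wrong way. The intervention section says "Walking, both purposive and incidental, will be specifically promoted as a physical activity option requiring no resources", and walking as travel is outside the recreational total. The documents do not support that reading, for four reasons.

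- Leaving travel out of a score labelled recreational is deliberate, and the transport total and the pedometer both register such walking. It is therefore wrong to say that no planned measure would show a net rise in walking.
- The intervention text does not mention transport. That incidental walking includes it is an inference.
- A fall in the recreational score needs assumed substitution. If recreational walking goes from 60 to 30 min and transport walking from 0 to 90, R falls by 30 and T rises by 90. Each total then reports its own domain correctly.
- Which activity measure ranks first, and whether there is an overall total, can be left to an analysis plan.

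**Conclusion.** The point holds as a defect of item wording. The separation made for walking was not made for cycling, so commuter cycling can enter the recreational total at weight 2 and the transport total at weight 1. For an assumed 100 min/week, the recreational score ranges from 0 to 200 with the reading of the item.

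The effect on the arm comparison is unknown. It depends on how many staff cycle to work, how they read the item, and whether either changes during the trial, and the documents give none of these. Self-reported activity is a secondary outcome, so the primary conclusions on well-being and depression are untouched. The finding rests on the article's description of the items matching the questionnaire in use. It is a minor correction, worth making because it is cheap beforehand and cannot be recovered afterwards.

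**What to change.** Word the vigorous item to exclude cycling as a means of travel, in parallel with the walking item, so that each minute enters one total only. If the questionnaire already says this, state it in the description of the measure. The wording should be settled before baseline and kept the same at all three assessments, since a change between them would itself shift the score.

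The cost is one phrase and no new data. The small downside is that the item moves slightly further from the source survey. An overall total from the five items is optional. If it is added, it needs the exclusion first, or it would carry any duplicated cycling minutes: 200 + 100 = 300 for the 100-minute rider who uses both items, against 0 + 100 = 100 with the exclusion.

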#### Mediating variables

The *READY *program targets five protective factors that will be evaluated as mediating variables. The conceptual relationship between these variables and outcome measures is presented in Figure 2.

**Figure 2 F2:**
[figure not shown]
**Conceptual meditational model**.

1. Positive emotions. The Positive and Negative Affect Schedule (PANAS-X) is widely used with well established psychometric properties [37]. We will use the ten items positive affect subscale. Respondents indicate on a five point Likert scale (1 *very slightly or not at all *to 5 *extremely*) how often they have felt each of ten feelings (e.g., enthusiastic, interested, determined).

2. Active Coping: The Brief COPE assesses 14 different coping strategies (e.g., humour, active coping and planning, denial and self blame, and behavioral disengagement) [38]. We will use the active coping subscales. Respondents indicate to what extent they use each of the specified strategies to try and cope with stress, using a four point Likert scale (0 *I haven't been doing this at all *to 3 *I've been doing this a lot*). The Brief COPE is comparable with the full COPE, and has acceptable levels of factorial validity and reliability [38].

3. Meaning. The Valued Living Questionnaire [39] will be adapted to exclude items assessing the importance of each life domain. Participants are asked to rate how consistent their actions have been in accordance with their life values for each of ten life domains (e.g., family relationships, community life) using a seven point Likert scale (1 *very inconsistent *to 7 *very consistent*).

4. Cognitive Flexibility. Two questionnaires will be used. The Mindful Attention Awareness Scale has 15 items to assess experiences of mindlessness in daily circumstances such as tasks and social interactions [40] using a six point Likert scale (1 *almost always *to 6 *almost never*. The scale has been shown to be reliable, valid, and sensitive to change [40]. The 10 item Acceptance and Action Questionnaire II assesses psychological flexibility and experiential avoidance using a seven point Likert scale (1 *never true *to 7 *always true*). Psychometric analyses indicate acceptable levels of factorial validity, criterion validity and reliability [29].

5. Social Support. Four items from The Brief COPE [38] will be used to assess use of emotional and instrumental support. Analyses of the Brief COPE [38] and the COPE [38] indicated that these four items loaded on a single factor [38], and had acceptable internal reliability.

#### Sociodemographic characteristics

Questionnaires will be used to assess gender, age, height, weight, educational qualifications, occupation, household composition, and gross annual household income.

#### Process measures

Participants' attendance at each session will be recorded by the interventionist, and the percentage attended of the total number of sessions will be calculated. Participants will be asked each week to rate their level of engagement with the home assignments for that session, using a five point Likert scale (1 *I was unable to do the homework this week *to 5 *I did all the activities*). At post intervention and follow-up, participants will be asked to provide feedback on their overall satisfaction with the program and materials, using a 5 point Likert scale (1 *strongly disagree *to 5 *strongly agree*) and open ended questions. To assess the fidelity of the intervention as delivered, two sessions by each interventionist will be videorecorded and rated by the program authors (NB, KP) for extent of adherence to the trainer's manual.

### Analyses

Data will be analyzed on an intention-to-treat basis, using random effects mixed modeling to examine group differences in the outcome measures among baseline, post-intervention and follow-up. Linear analyses will be used to examine the potential mediation of the five identified protective factors (see Figure 2). We will calculate the (a) direct effect of the program on the outcome measures (τ); (b) effect of the intervention on each of the mediating variables, adjusted for baseline values (α); (c) the effect of the residual change score (post intervention score adjusted for the baseline score) of the proposed mediating variables on the outcome measures, after adjustment for the intervention (β); and then examine whether there is attenuation or change in significance in the relationship between the intervention and the outcome measures, after adjustment for the change in the mediating variables (τ'). The product of the α and β coefficients will be used to provide an estimate of the magnitude of the mediation effect in the units of the outcome variable, and the 95% confidence intervals of the point estimates of the mediated effects will be examined to test for mediation [41].

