**Methods/Design:**

In a cluster randomized trial, 95 participants will be allocated to either a waitlist or one of two intervention conditions. Both intervention conditions will receive a 10 × 2.5 hour group resilience training program (*READY*) over 13 weeks. The program targets five protective factors identified from empirical evidence and analyzed as mediating variables: positive emotions, cognitive flexibility, social support, life meaning, and active coping. Resilience enhancement strategies reflect the six core Acceptance and Commitment Therapy processes (values, mindfulness, defusion, acceptance, self-as-context, committed action) and Cognitive Behavior Therapy strategies such as relaxation training and social support building skills. Sessions include psychoeducation, discussions, experiential exercises, and home assignments. One intervention condition will include an additional session and ongoing content promoting physical activity. Measurement will occur at baseline, two weeks post intervention, and at eight weeks follow-up, and will include questionnaires, pedometer step logs, and physical and hematological measures. Primary outcome measures will include self-reported indicators of psychosocial well-being and depression. Secondary outcome measures will include self-reported indicators of stress, anxiety and physical activity, and objective indicators of CHD risk (blood glucose, cholesterol [mmol·L^-1^], triglycerides, blood pressure). Process measures of attendance, engagement and fidelity will also be conducted. Linear analyses will be used to examine group differences in the outcome measures, and the product of coefficients method will be used to examine mediated effects.

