## Methods/Design

### Study Design

Figure 1 provides an overview of the study process. This is a cluster randomized trial with two intervention conditions and a wait list group. Participants in one intervention condition will receive the psychosocial resilience training program (*READY*). Participants in the other intervention condition will also receive the resilience training program, as well as additional content promoting physical activity. Measurements will take place at baseline, two weeks post intervention and after an additional eight weeks, and will include questionnaires, pedometer step logs, physical measures and hematological data. The study protocol was approved by The University of Queensland Medical Research Ethics Committee (2007000303).

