### Participants and Randomization

Participants will be volunteers recruited from staff of the Townsville district of the State Government Department of Education and Training. The study will be advertised using information sessions and email lists, and potential participants will submit a written expression of interest. Respondents will be initially screened over the telephone by a research assistant to exclude those who (a) are currently receiving psychiatric/psychological treatment (counseling or pharmacological) or who have previously been diagnosed with a major psychiatric disorder (e.g. schizophrenia), or (b) have a medical condition which contraindicates physical activity participation as suggested by the 2005 Sports Medicine Australia screening guidelines [26].

Eligible respondents will be provided with study details, and those who provide verbal consent will be scheduled for baseline assessment. Participants attending baseline assessment will receive written and verbal information on the study requirements and asked to provide written consent before any data are collected. After baseline assessment, participants will be clustered by occupation (teachers/teacher aides, management/senior staff, administration/support staff) and geographical location (Townsville City, Regional). Each cluster will be randomly allocated to one of the three study conditions by a research assistant simultaneously drawing clusters and conditions out of two separate containers.

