### Sample Size

The sample size is based on detecting a difference in personal well being as measured by Ryff's Scales of Psychological Well-Being [27]. Previous research showed that differences of 3.0 points (SD 4.0) can be detected post intervention [28]. To achieve a similar difference, using a two tailed test with alpha level 0.05 and power of 80%, we will require 28 participants in each of the three groups. Allowing for attrition, we will aim to recruit 30-35 participants per condition.

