Mid Program Review Resilient and non resilient characteristics, activating and trouble shooting coping strategies.	Active coping
Life Values and Meaningful Action About values, value identification, meaningful action.	Life meaning
Social Connectedness Types of support, support responses, active and reflective listening, barriers to social connectedness.	Social support
Relaxation and Pleasant Activities Active relaxation exercises, progressive muscle relaxation exercises, pleasurable activities.	Positive emotions
Review and Planning for the Future Resilient and non resilient characteristics, activating and trouble shooting coping strategies.	Active coping

Note. Although different themes are identified for each session, the content in each session is referred to and followed up in subsequent sessions, so as to integrate the material across sessions.

The program will be implemented as 10 × 2.5 hour sessions over 13 weeks (one school term and two weeks of school holidays). Sessions will be in a group format with 10-20 participants per group, and will be led by an experienced psychologist. A detailed trainer's manual has been prepared including learning objectives, outlines, learning activities, handouts and audiovisual materials for each session. Interventionists will be trained by the program authors (NB and KP).

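### The Analyses section names the randomised cluster in neither the mixed model nor the mediation analyses, although at most six clusters are allocated to three arms

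*Protocol article*

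**What the plan says.** The Study Design section of the protocol article declares: "This is a cluster randomized trial with two intervention conditions and a wait list group". Under Participants and Randomization, "participants will be clustered by occupation (teachers/teacher aides, management/senior staff, administration/support staff) and geographical location (Townsville City, Regional", and then "Each cluster will be randomly allocated to one of the three study conditions". Three occupation categories by two locations give at most six clusters. The Abstract gives the size: "95 participants will be allocated to either a waitlist or one of two intervention conditions".

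The Analyses section plans intention-to-treat analysis "using random effects mixed modeling to examine group differences in the outcome measures among baseline, post-intervention and follow-up". It does not say at what level the random effects sit. On mediation it says: "Linear analyses will be used to examine the potential mediation of the five identified protective factors". It then sets out τ, α, β, τ′ and the interval for the product αβ in some detail, without a cluster term.

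The Sample Size section starts from the statement that "differences of 3.0 points (SD 4.0) can be detected post intervention" and arrives at 28 per group, with no ICC or design effect. On delivery, the Group 1 section adds: "Sessions will be in a group format with 10-20 participants per group". The Discussion mentions clustering only as something that may reduce contamination.

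**The concern.** People in the same occupation and location are likely to resemble one another, and they are allocated together. An arm contrast therefore carries between-cluster variance, which a participant-level analysis does not count. With about two clusters per arm there is little averaging of that variance, and chance differences between occupations or locations can reach significance as apparent program effects.

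At stake are the two primary outcomes, the comparison of READY with READY plus physical activity, and the mediation claims. The coefficient α is itself an arm contrast, so its interval would tend to be too narrow, and through it the interval for αβ.

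This is more than omitted detail. The article spells out its mediation steps and its sample size, and neither refers to the unit that was randomised.

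**Working it through.** **1. Reproduce the plan's figure.** Inputs from Sample Size: difference 3.0, SD 4.0, two-sided alpha 0.05, power 80%.

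n per group = 2 × (1.960 + 0.842)² × (4.0/3.0)² ≈ 27.9, rounded up to 28. Power at 28 is 80.1% by the normal approximation. An exact t-test would need 29, which is close enough. The figure of 28 is reproduced as an individually randomised two-group calculation, that is, with a design effect of 1.

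**2. Cluster size.** 3 × 2 = 6 clusters at most; 95/6 = 15.8 participants each. Equal sizes and two clusters per arm are assumptions.

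**3. Error rate if clusters are ignored.** Design effect DE = 1 + (15.8 − 1) × ICC. True two-sided error = 2 × [1 − Φ(1.96/√DE)]. The documents give no ICC, so a range is assumed. The simulated column is a participant-level t-test between two arms in 20,000 trials with clusters of 16.

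| ICC (assumed) | DE | Naive SE as share of correct SE | True error, formula | Simulated |
|---|---|---|---|---|
| 0 | 1.00 | 100% | 5.0% | 4.8% |
| 0.01 | 1.15 | 93% | 6.7% | 6.8% |
| 0.02 | 1.30 | 88% | 8.5% | 8.6% |
| 0.05 | 1.74 | 76% | 13.7% | 14.2% |
| 0.10 | 2.48 | 63% | 21.4% | 22.4% |

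**4. Change from baseline.** A cluster effect that is constant over time cancels. With a share c of the cluster variance constant and an assumed within-person correlation of 0.6, the ICC of the change score is ICC(1 − c) / [ICC(1 − c) + (1 − ICC)(1 − 0.6)]. With c = 0.5 and ICC 0.05 this is 0.025/(0.025 + 0.380) = 0.062. Simulated error at ICC 0.01, 0.05 and 0.10:

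- c = 1: 5.0%, 5.0%, 5.0%
- c = 0.8: 6.2%, 9.8%, 14.5%
- c = 0.5: 7.0%, 16.2%, 26.0%

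**5. A cluster term alone is not enough.** Six clusters less three arms leave 3 degrees of freedom. A valid cluster-level statistic on 3 df that is referred to ±1.96 rejects about 14.5% of the time under no effect. Referred to t on 3 df, it held about 5% in simulation at every ICC tried.

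**6. Power of the valid test.** For d = 3.0/4.0 = 0.75 with 32 per arm, the cluster-mean test with variance pooled over the three arms (3 df) has simulated power of 53%, 49%, 35% and 26% at ICC 0, 0.01, 0.05 and 0.10.

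No calculation was made for β or for αβ. The mediator varies within clusters, so the design effect of an arm contrast does not carry over to β.

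**The case against.** The strongest reply is that the article is silent rather than wrong. A reader might infer that the random effects are for repeated occasions only, that mediation is ordinary regression, and hence that standard errors will be too small and the error rate well above 5%. The text does not support that. The three occasions qualify the group differences, not the random effects, whose level is left open and could include the cluster. The Abstract uses the phrase linear analyses for the group comparison too, so the same phrase does not rule out a mixed model for mediation. How far the error exceeds 5% depends on an ICC that the documents do not give: at 0.01 the excess is small. Stable occupational or regional differences could largely cancel in change contrasts. All of this stands, and the point is therefore conditional.

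It can also be said that degrees-of-freedom methods belong in an analysis plan. That holds for the choice of method. It does not hold for whether the analysis respects the unit of allocation, particularly as the sample size demonstrably does not.

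Baseline adjustment is only a partial defence. Effects of sharing a training group arise during the 13-week program, after baseline. Against blaming trainers in particular, the Discussion has interventionists work in both READY conditions.

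**Conclusion.** The point holds in conditional form. Neither analysis names the randomised cluster, and the sample size assumes independent participants. If the cluster is left out, uncertainty in the arm contrasts is understated. The inflation is slight at ICC 0.01, and material from about 0.02 upwards. Contrasts of change are protected only so far as cluster effects stay constant over time.

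These sizes rest on an assumed ICC, six equal clusters and two per arm; the change-score figures also rest on the assumed within-person correlation and the share of cluster variance that is constant. Unequal clusters would raise the design effect. For mediation, the direction is clear for α and, through it, for αβ; the effect on β is not quantified. The problem is one of understated uncertainty; no systematic bias in the effect estimate is claimed.

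**What to change.** State in the Analyses section that:

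- every outcome and mediation model includes a random intercept for the randomised occupation-by-location cluster, with a cluster-by-time term for change contrasts where it can be estimated;
- arm contrasts, including α, are tested on between-cluster degrees of freedom, for example by Kenward-Roger or by cluster means with about 3 df;
- β is estimated at participant level in a model with the same cluster term, because cluster means cannot supply it.

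Treat training group as a sensitivity term only, and only where it differs from the cluster. With clusters of about 16 and training groups of 10 to 20, the two may largely coincide and not be separable.

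The edit itself is short, but it is not free. Intervals will be wider, and power at d = 0.75 is about 53% at ICC 0, 35% at 0.05 and 26% at 0.10 instead of 80%. The Sample Size section should restate the power on this basis. The shortfall comes from having at most six clusters, and the corrected analysis only makes it visible.
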